#### Laparoscopic procedure

Preoperative insertion of nasogastric tube is performed depending on each surgeon’s discretion. Prophylactic antibiotics are injected within 30 minutes before skin incision. The location and number of trocars are not limited. Surgeons will examine the abdominal cavity to determine whether there is no metastatic lesion or if the gastric cancer is resectable. If the patient has unexpected metastatic lesions or the surgeon decides that curative resection of tumor is impossible, the operation is stopped and the patient is excluded from this RCT. Washing cytology could be performed by inserting 50 cc of saline solution into the pelvic cavity. Then, the surgeon begins the D2 lymphadenectomy including total omentectomy. The guideline for D2 lymphadenectomy in locally AGC patients is shown in Table 1. If surgeons make an additional abdominal incision to control bleeding or for any other reason before finishing the laparoscopic D2 lymphadenectomy, they will record this situation as “conversion to open” in the eCRF system. After lymphadenectomy, the reconstruction methods are not limited in this RCT. The surgeon can perform one of the Billroth-I, Billroth-II, or Roux-en Y methods for reconstruction, which can be carried out by minilaparotomy. Hand-sewing or using staplers for anastomosis are not limited, and drain insertion is left to the discretion of each surgeon.

**Table 1 Tab1:** **Guidelines forof D2 lymph node dissection for locally advanced gastric cancer**

1. Total omentectomy	4d
2. Division of the left gastroepiploic artery	4sb
3. Appropriate extent of No. 6 lymph node (LN) dissection	6
4. Appropriate extent of No. 5 LN dissection	5
5. Appropriate extent of No. 12a LN dissection	12a
6. Appropriate extent of No. 8a LN dissection	8a
7.Appropriate extent of No. 9 LN dissection (resection of the celiac plexus is not necessary)	9
8. Appropriate extent of No. 7 LN dissection	7
9. Appropriate extent of No. 11p LN dissection	11p
10. Prevention of pancreatic injury during suprapancreatic LN dissection	
11. Appropriate extent of No. 1 and 3 LN dissection	1, 3

LN, lymph node.

#### Open conventional procedure

The open surgery procedure is similar to that of laparoscopic surgery, with the exception of lymphadenectomy performed under direct view.

#### Postoperative care

The ward staff will evaluate the patients every morning and afternoon for the presence of any issues affecting the patients’ recovery. The degree of pain, diet schedule, and gas out were daily recorded until discharged, and laboratory findings are recorded on the first and fifth postoperative day. After surgery, the surgeon can progress the diet schedule from sips of water to a soft diet according to the patient’s condition. If the patients are in good condition 2 or 3 days after starting a soft diet and do not have complaints regarding their status, they can be discharged from the hospital.

After fully recovering from surgery, patients diagnosed with Stage II (except T1) or Stage III cancer in the final pathology report will be recommended for adjuvant chemotherapy based on 5-fluorouracil administration. Adjuvant chemotherapy will be started from 4–6 weeks postoperatively, if the patients’ general condition is suitable for chemotherapy.

After curative resection, all patients will be regularly evaluated for disease recurrence postoperatively every 3 or 6 months over a 3-year period. Abdominopelvic computed tomography (CT), serum tumor markers (CEA and CA19-9), and other parameters can be included in studies for regular follow-up.

### Participating surgeons and quality control

To participate in this RCT, surgeons will be validated through a separate clinical study (registered at www.clinicaltrials.gov as NCT01283893). Surgeons submit unedited videos of their laparoscopic and open conventional D2 lymphadenectomy procedures, which are reviewed by international experts. Finally, the review committee decides whether the surgeons are validated and can join the RCT.

After starting recruitment in this RCT, surgeons will record an unedited video of the laparoscopic operation and a photo of the open surgery for every 10 recruitments. The steering committee can request submission of these data for evaluation of safety of surgeons showing frequent severe side effects.

### Outcome measurements

The primary endpoint of the KLASS-02 RCT is non-inferiority in the 3-year relapse-free survival rate after laparoscopic subtotal gastrectomy and extended lymphadenectomy for locally AGC compared with open conventional surgery. To measure this endpoint, the criteria for recurrence are suggested in detail. Recurrence can be detected on regular follow-up studies such as abdominopelvic CT in patients without specific symptoms through a formal radiology report. If the results of follow-up studies are suspicious, whole-body positron emission tomography-CT, magnetic resonance imaging of the liver, or laparoscopic exploration can be performed to confirm recurrence. Otherwise, patients can attend follow-ups at shorter intervals than the planned schedule. Patients with specific symptoms, such as abdominal mass, weight loss, or intestinal obstruction, which might coincide with recurrence, should be evaluated for recurrence immediately regardless of the follow-up schedule. Surgeon should report recurrence in enrolled patients by entering this information into the eCRF as soon as the recurrence is confirmed.

Secondary outcomes include postoperative morbidity and mortality, postoperative recovery, and quality of life. Complications are divided into early and late morbidities depending on time of occurrence. Early morbidity is defined as surgery-related complications occurring within 21 days postoperatively, and includes the events listed in Table 2. Complication severity is classified according to grading system suggested by Dindo D et al. [10]. Regarding postoperative morbidity, the operative time and blood loss volume are also recorded. In cases of conversion from laparoscopic to open surgery, the reason for conversion should be explained. The events related to late morbidity, which occur after the 28th postoperative day, are listed in Table 2.

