### Sample size calculation

The primary endpoint of this RCT is 3-year relapse-free survival of patients diagnosed with locally AGC. In an RCT conducted by Sakuramoto et al. [9], the 3-year relapse-free survival of gastric cancer patients who received TS-1 adjuvant chemotherapy and were diagnosed with stage II or III cancer on pathology from curative gastrectomy with D2 lymph node resection was 72% (hazard rate = 0.11). Therefore, the hazard rate of patients who underwent open conventional surgery in the control condition was 0.11 in the 3 year. In addition, the margin of non-inferiority assumed a hazard ratio (HR; hazard rate of group A/hazard rate of group B) of 1.43 according to the study design in the Sakuramoto et al., in which the HR of the surgery-only group was compared with that of the adjuvant group. The null hypothesis was assigned as HR ≥ HR_0_, and the alternative hypothesis as HR < HR_0_. Type I error was set at 0.25 (one-sided) with 90% power, and the sample size was calculated using the log-rank test for non-inferiority (PASS 12. NCSS, LLC. Kaysville, Utah, USA. www.ncss.com.).

As a result, a total of 1,050 patients (525 patients per group) with 330 target event as recurrence are required when we consider a 10% dropout rate.

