## Discussion

To the best of our knowledge, this study is the first multicenter randomized clinical trial recruiting a large number of patients to compare laparoscopic D2 lymphadenectomy with open conventional lymphadenectomy in patients preoperatively diagnosed with locally AGC. Through this clinical trial, we aim to show the non-inferiority in the 3-year relapse-free survival rate of patients undergoing laparoscopic procedures compared with open surgery as the primary end point. In addition, laparoscopic surgery is expected to show comparable surgical outcomes such as morbidity and mortality, and improved postoperative recovery. Particularly, we sought to design the trial to overcome the challenges confronting surgical clinical trials while following the general principles of multicenter RCTs.

In general, multicenter RCTs should be designed according to specific principles such as evidence-based calculation of sample size, concealment of randomization, interim analysis, ITT analysis, and blinding to the type of intervention to avoid bias. Our protocol was established by following these general principles as closely as possible. However, blinding of the surgeons and patients to the intervention is impossible in most surgical clinical trials. In particular, when comparing laparoscopic surgery with conventional laparotomy as in the present RCT, blinding between 2 surgical procedures cannot be achieved due to the technical difficulty. In some previous surgical RCTs, postoperative dressings were applied using the same methods for patients who underwent both laparoscopic and open cholecystectomy, thus the type of intervention was blinded to patients and ward staff [14,15]. However, it is unlikely that perfect blinding using the same dressing is achieved, and blinding patients to the type of surgery might cause ethical issues. Non-blinding of staff investigating the outcomes will likely cause subjective measurement of them. To minimize the bias due to non-blinded randomization in the present RCT, we suggested the objective outcomes as endpoints. Therefore, the criteria for recurrence, the primary endpoint of this RCT, were described in detail.

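### The primary endpoint is stated as a 3-year relapse-free survival rate, but the hypothesis, margin and event target are all for a hazard ratio, and no sentence says which decides

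*Protocol article*

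**What the plan says.** *Outcome measurements*: "The primary endpoint of the KLASS-02 RCT is non-inferiority in the 3-year relapse-free survival rate". The *Discussion* repeats the aim: "we aim to show the non-inferiority in the 3-year relapse-free survival rate of patients undergoing laparoscopic procedures". Both name a proportion at one time point.

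*Sample size calculation* drops the word rate: "The primary endpoint of this RCT is 3-year relapse-free survival of patients diagnosed with locally AGC". It takes the control value from a cited adjuvant chemotherapy trial in pathological stage II or III disease: "gastrectomy with D2 lymph node resection was 72% (hazard rate = 0.11" per year. It then moves to the hazard scale: "the margin of non-inferiority assumed a hazard ratio (HR; hazard rate of group A/hazard rate of group B) of 1.43", with the hypotheses "The null hypothesis was assigned as HR ≥ HR_0_, and the alternative hypothesis as HR < HR_0". The size comes from a log-rank non-inferiority calculation and gives 330 events and 1,050 patients, 525 per group, allowing 10% dropout. The printed error level is "Type I error was set at 0.25 (one-sided) with 90% power".

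The closing paragraph of *Patient groups for statistical analysis* names Kaplan-Meier curves with log-rank tests for relapse-free survival, at a 5% level. It names no comparison of 3-year rates and no confidence limit to set against a margin. *Postoperative care* describes surveillance for recurrence over 3 years.

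**The concern.** A non-inferiority claim is defined by a quantity and a margin on the same scale. Here the quantity in the endpoint sentence is a 3-year rate, and the margin belongs to a hazard ratio. The two are linked only through proportional hazards and one particular control rate, and the article does not say that the margin should be carried across that link or how. The analysis paragraph does not settle it: an unqualified log-rank test at 5% is normally a test of no difference and does not refer to 1.43.

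At stake is which number decides the trial. If the rate were taken as decisive, someone would have to supply a margin in percentage points, possibly after results are known. The natural choice, the planning drop, becomes more lenient than the stated margin when control survival is above 72%. That is plausible: the 72% comes from pathological stage II or III patients, whereas eligibility is clinical cT2 to cT4a including node-negative disease, and *Postoperative care* recommends chemotherapy only for a subset defined by final pathology.

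**Working it through.** **Inputs.** Control 3-year survival 72%, margin 1.43, 90% power, 1,050 patients, 10% dropout, 330 events (all from *Sample size calculation*). Evaluable patients: 1,050 × 0.9 = 945, about 472 per group. The accrual period is not given. Control rates of 80% and 85% are assumptions.

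**1. The plan's own figure.** Events = 4(z_α + z_β)² / (ln 1.43)², with ln 1.43 = 0.3577.
- One-sided 0.025: 4(1.960 + 1.282)² / 0.1279 = 329, which matches 330.
- One-sided 0.05: 268.
- One-sided 0.25, as printed: 120.

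The 330 events therefore belong to a hazard-ratio test at one-sided 0.025. That level is used below.

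**2. The margin on the rate scale.** Under proportional hazards the laparoscopic rate at the margin is S₀^1.43. At S₀ = 0.72 this is 0.625, a drop of 9.5 points.

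**3. Agreement at the planning values.** A rate design with that margin needs 10.51 × 2 × 0.72 × 0.28 / 0.0948² = 471 per group, or 524 after 10% dropout. That is 1,048 in all, against the stated 1,050. In simulation (472 per group, exponential times, follow-up stopped at 3 years, 3,000 trials per setting), with control at 72%:
- True hazard ratio 1.43: the hazard-ratio rule passes in 2.5% and a 9.5-point rate rule in 2.2%.
- True hazard ratio 1: the two verdicts differ in about 8%.

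**4. Away from 72%.**

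| Control rate | Drop equal to HR 1.43 | HR equal to a fixed 9.5-point drop |
|---|---|---|
| 72% | 9.5 points | 1.43 |
| 80% | 7.3 points | 1.57 |
| 85% | 5.7 points | 1.73 |

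**5. Different data.** With 72% in both groups, events by 3 years are 945 × 0.28 = 265, or 1,050 × 0.28 = 294 with no dropout. Reaching 330 needs an event fraction of 330/945 = 34.9%, or 330/1,050 = 31.4%. At a hazard of 0.11 per year, that is a common follow-up of −ln(0.651)/0.11 = 3.9 years or −ln(0.686)/0.11 = 3.4 years. With an assumed 2-year accrual plus 3 years of further follow-up, the hazard-ratio design gives 1,034 patients, near the stated 1,050, so the sizing is consistent with counting events after year 3. A 3-year rate does not use those events.

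**6. Power if data stop at 3 years.** √(265/4) × 0.3577 − 1.960 = 0.951, which is 83% power instead of 90%.

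**The case against.** The strongest reply is that the decision rule already sits on one scale. The hypotheses, the margin, the sizing test and the event trigger for the interim analysis are all in hazard or event terms, and no rate hypothesis is written anywhere. The sample size section itself turns 72% into a hazard, so 3-year survival can be read as a loose name for the endpoint, and the exact success criterion is often left to the analysis plan. Much of this stands: a careful reader would probably conclude that the hazard ratio governs. It does not remove the mismatch, because the article states both the quantity and the margin itself, on different scales, and puts the rate in the sentence that defines the endpoint.

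A reader might go further and infer that the plan contains two competing success rules likely to give opposite verdicts. The documents do not support that. The 9.5-point rule is derived here and appears nowhere in the article. At the planning values the verdicts mostly agree. Large disagreement under no true difference (27% of simulated trials at 80% control survival, 41% at 85%) needs assumed control rates and follow-up stopped at 3 years. With an assumed 3-year accrual and at least 3 years of follow-up, it falls to 12.6% and 26%.

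**Conclusion.** The point holds as a mismatch between the stated endpoint and the stated test. The endpoint is a 3-year rate with no margin of its own, and the only margin, hypothesis and event target are for a hazard ratio. At the planning 72% the practical gap is small: false-pass rates near 2% on either scale, with verdicts differing in about 8% of simulated trials under no true difference. It would matter more if control survival were higher. At an assumed 80% to 85%, a fixed 9.5-point reading would tolerate hazard ratios of 1.57 to 1.73 against the stated 1.43. Separately, a 3-year endpoint and a 330-event target call for different lengths of follow-up.

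These results rest on proportional hazards, exponential times, a one-sided 0.025 level in place of the printed 0.25, and 10% of patients lost. The 330-event shortfall at 3 years also assumes no true difference between groups.

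**What to change.** Keep the hypothesis in *Sample size calculation* and make it the sole decision rule. Declare non-inferiority if the upper limit of the two-sided 95% confidence interval for the laparoscopic/open hazard ratio of relapse-free survival is below 1.43, analysed at the planned 330 events. State the level as one-sided 0.025, which reproduces the 330. Reword the endpoint in the *Abstract*, *Outcome measurements* and *Discussion*, and the test in the closing paragraph of *Patient groups for statistical analysis*, to match. Report the 3-year Kaplan-Meier difference with its confidence interval as supportive, and say that it does not decide.

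Do not censor at 36 months unless the power is restated: about 83% at a 72% control rate with 945 evaluable patients. Keeping 330 events under that censoring would need 330/0.28 = 1,179 evaluable patients, or about 1,310 randomised (1,179/0.9), some 260 more than planned.

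Cost: wording only, if made before outcome data are seen, and no extra patients. The rate reading can no longer decide, and reaching 330 events needs follow-up beyond 3 years or a restated power.

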### Study protocol

The Ajou ARO (Academic Research Organization) in Ajou University Hospital will manage this clinical trial. As soon as the participating surgeons obtain informed consent from the patients, researchers entered the patient information into an web-based electrical clinical report form (eCRF;http://clintrial.ajoumc.or.kr/klass02/). The beta version of eCRF system tested at each actual site before full implementation, to ensure data capture system and to reduce user error. The eCRF system is automatically given screening number according to the sequence in which the informed consent forms are received. And if patients meet the criteria for a randomization, then eCRF system assigned at each surgery group.. Finally, the system provides an allocation number with a pre-generated randomized code for those who are selected by inclusion and exclusion criteria. A randomized block design is applied for randomization with each investigator as the stratification factor (R 2.10.1). To maintain the properties of randomization, block size is not open to the investigators. The surgeons are immediately notified of the randomization results via e-mail. After notification, the surgeons let the patients know which type of operation they will undergo. Therefore, the surgeon and patient blinding is impossible owing to the nature of surgical RCT. However, the protocol recommends that ward staff members evaluating patient outcomes be blinded, if possible. If the surgeon does not perform the operation within 30 days after recruitment, the patients are excluded from the trial. These patients will need to be re-evaluated for re-recruitment into this RCT.

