**Table 2 Tab2:** **Classification of morbidity in the present study**

Early morbidity	Late morbidity
0: No complications	1: Intestinal obstruction
1: Wound infection	2: Stenosis
2: Fluid collection or abscess	3: Chronic wound complications
3: Intra-abdominal bleeding	4: Others
4: Intraluminal bleeding	
5: Postoperative ileus	
6: Anastomosis stenosis	
7: Leakage	
8: Pancreatitis or fistula	
9: Pulmonary	
10: Urinary	
11: Renal	
12: Hepatic	
13: Cardiac	
14: Endocrine	
15: Others	

To evaluate overall survival as one of the oncologic outcomes and surgery-related mortality, all deaths of recruited patients during the RCT will be reported immediately, and the cause of death will be recorded.

For postoperative outcomes designated as secondary endpoints, the postoperative diet schedule, recovery of bowel movements, and pain scale will be investigated every morning before hospital discharge. Serum levels of whole blood leukocytes, hemoglobin, amylase, creatinine, and albumin are recorded as biochemical outcomes twice during recovery. Finally, the length of hospital stay and readmission will be evaluated.

To investigate the quality of life, the questionnaire suggested by the European Organization for Research and Treatment of Cancer (EORTC) will be used with web-based permission from EORTC. Patients are requested to complete the EROTC-QLQ 30 and STO 22 questionnaires perioperatively and at 4 weeks and 1 years postoperatively.

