The safety of laparoscopic D2 lymphadenectomy should be emphasized, because this study is the first multicenter RCT to evaluate its efficacy. In our RCT, morbidities related to surgeries will be investigated separately during early and late postoperative periods after surgery. Since most late complications such as reflux and intestinal obstruction are mainly related to reconstruction methods regardless of the type of laparoscopic or open laparotomy, we eventually focused on early postoperative morbidity to evaluate safety. When the number of patients recruited in this RCT reaches 484, the data related to early postoperative morbidities will be analyzed to determine whether laparoscopic surgery for D2 lymphadenectomy is less safe compared with open surgery. The number of patients required for this safety analysis was calculated according to previous RCTs, which reported that the complication rate of D2 lymphadenectomy was 20.9% in an RCT performed by Japanese surgeons, and the limitation of non-inferiority for complications of D2 lymphadenectomy compared with D1 was 12.0% in another Italian RCT [11,25]. This protocol includes a plan to stop recruitment and discontinue this RCT if the results of the safety analysis show significant inferiority in the safety of laparoscopic groups relative to the conventional group.

In conclusion, the KLASS-02 RCT was designed to show the efficacy of laparoscopic D2 lymphadenectomy in AGC patients compared with the open procedure. We attempted to highlight the principle of surgical clinical trials, and the internal validity of surgeons participating in this RCT was considered. Finally, we hope to suggest our RCT to other researchers who wish to conduct a well-designed, organized surgical clinical trial.

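### Early morbidity counts only complications judged related to surgery; in an open-label trial this lets attribution shift the comparison used for the 484-patient safety decision

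*Protocol article*

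**What the plan says.** Under Outcome measurements the protocol article defines the outcome: "Early morbidity is defined as surgery-related complications occurring within 21 days postoperatively, and includes the events listed in Table 2". Table 2 then lists fifteen types of event. Some are local to the operation, such as wound infection, bleeding and leakage. Others are systemic: pulmonary, urinary, renal, hepatic, cardiac, endocrine and a residual category. Severity is graded on a published scale.

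On blinding, the Study protocol section says: "Therefore, the surgeon and patient blinding is impossible owing to the nature of surgical RCT". For those who assess outcomes it adds: "However, the protocol recommends that ward staff members evaluating patient outcomes be blinded, if possible".

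The Discussion says of the safety evaluation: "we eventually focused on early postoperative morbidity to evaluate safety". Under Safety assessment for early morbidity, 242 patients per group are planned from a complication rate of 20.9%, a non-inferiority margin of 12 percentage points, one-sided type I error of 0.025 and 90% power. At 484 patients the steering committee uses the result to decide whether the trial goes on. Morbidity is also a secondary outcome.

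For deaths, the text after Table 2 gives the purpose as "To evaluate overall survival as one of the oncologic outcomes and surgery-related mortality" and the rule as "all deaths of recruited patients during the RCT will be reported immediately, and the cause of death will be recorded".

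**The concern.** As worded, a complication must pass a relatedness test before it counts. For leakage or a wound infection the test is a formality. For a pneumonia, a cardiac event or a rise in creatinine it is an opinion, and the person holding it may know which operation was done. If such events are set aside somewhat more readily after laparoscopy, the laparoscopic complication rate falls and the comparison moves towards non-inferiority, the conclusion the trial hopes to reach.

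Randomisation makes the test unnecessary. Complications unconnected with the operation fall on both arms by chance alone, so leaving them in adds some noise but no systematic difference. Taking them out by judgement opens a route for bias. The Discussion recognises the general hazard: "Non-blinding of staff investigating the outcomes will likely cause subjective measurement of them". The remedy it names is objective endpoints, and its example is the recurrence criteria. A relatedness condition on morbidity points the other way.

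**Working it through.** **Inputs.** From Safety assessment for early morbidity: open rate 0.209, margin 0.12, one-sided alpha 0.025 (z = 1.960), power 90% (z = 1.2816), 242 per group. The numbers of points discounted as unrelated are assumptions.

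**1. The plan's own figure.** Non-inferiority of two proportions with equal true rates and unpooled variance:

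n = 2 × 0.209 × 0.791 × (1.960 + 1.2816)² / 0.12² = 241.3, rounded up to **242 per group**.

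Power at 242: SE = √(2 × 0.209 × 0.791 / 242) = 0.03696, and Φ(0.12/0.03696 − 1.960) = 90.1%. The planned size is reproduced, so there is no numerical error.

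**2. Discounting in the laparoscopic arm only.** Put the true laparoscopic rate at the limit of what is acceptable, 0.209 + 0.12 = 0.329. Let pL be the rate left after events are set aside.

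SE = √[(0.209 × 0.791 + pL(1 − pL)) / 242]

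P(margin wrongly met) = Φ((0.12 − (pL − 0.209))/SE − 1.960)

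| Points set aside | pL | SE | P(margin wrongly met) |
|---|---|---|---|
| 0 | 0.329 | 0.03994 | 2.5% |
| 1 | 0.319 | 0.03976 | 4.4% |
| 2 | 0.309 | 0.03957 | 7.3% |
| 3 | 0.299 | 0.03936 | 11.5% |

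Two points is 0.02/0.329, about 6% of laparoscopic complications, or about 5 patients of 242.

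**3. Same share removed from both arms.** The margin is an absolute difference, so even-handed discounting also narrows the gap. Removing 5%, 10% or 20% of complications from each arm leaves true differences of 11.4, 10.8 and 9.6 points. The same formula then gives 3.5%, 5.0% and 9.5%. These count as errors only if the 12 points were meant for all complications.

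**4. The stopping wording in the Discussion.** That section ties stopping to significant inferiority of laparoscopy, which is not the same test as meeting the margin. If it is read as a one-sided 0.025 test of no difference, the chance of detecting a true 12-point excess is Φ((pL − 0.209)/SE − 1.960). For 0, 1, 2 and 3 points set aside this is 85%, 79%, 71% and 63%. The direction is the same: discounting hides harm.

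**5. Effect of the remedy on power.** If counting all complications raised the common rate to an assumed 25%, n = 2 × 0.25 × 0.75 × (1.960 + 1.2816)² / 0.12² = 273.6, or 274 per group. At 242, SE = √(0.375/242) = 0.03936 and power is Φ(0.12/0.03936 − 1.960) = 86%.

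**The case against.** The strongest reply is that the phrase may be only a general label for postoperative complications, with Table 2 as the working list. The article describes no causality field and no causality judgement. It is also a condensed account, and the full protocol may hold event criteria or adjudication rules. This lowers confidence that the filter operates in practice. It does not change the wording: the sentence is offered as the definition, and taken literally it excludes events judged unrelated.

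A reader might infer that unblinded surgeons make this judgement. The documents do not say so. They name nobody, and they recommend blinded ward assessors where feasible. What can be said is that nothing in the article requires whoever assesses relatedness to be unaware of the arm.

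A reader might also infer that deaths are filtered in the same way. They are not. The secondary outcome is postoperative morbidity and mortality with no qualifier, and every death is reported with its cause. Surgery-related mortality is one quantity drawn from complete data, so an all-cause comparison remains available.

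Three further points stand in part. Many Table 2 events leave little room for discretion, so the exposure lies mainly in the systemic and residual categories. The remark in the Discussion about unblinded staff concerns measurement in general, not relatedness. And whether a complication occurred at all would still be assessed open-label after any change of definition.

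**Conclusion.** The point holds for early morbidity and is worth correcting. The definition contains a subjective condition, the trial is open-label, assessor blinding is optional, and the outcome informs a decision on whether the trial continues. The planned 242 per group is correct on its own assumptions.

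The size is illustrative. With a true rate of 32.9% against 20.9%, setting aside 1 to 3 points in the laparoscopic arm only moves the false non-inferiority rate from 2.5% to between about 4.4% and 11.5%. This assumes that the true difference sits exactly at the margin and that discounting is one-sided. The documents give no attribution rates, so the figures show sensitivity and are no evidence that bias has occurred.

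**What to change.** Define early morbidity as any complication in the stated postoperative window, whatever its judged relation to surgery. Use that count for the 484-patient analysis and for the morbidity outcome. Keep relatedness as a recorded, descriptive item that does not decide whether an event is counted. For mortality, at most report all-cause postoperative death beside surgery-related mortality.

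The cost is a change of wording and possibly one instruction in the electronic case report form, since only deaths are stated to be captured regardless of relatedness. The observed complication rate may exceed 20.9%, with some loss of power (about 86% at 242 per group if it were 25%). The change removes the attribution step only; blinded assessment of whether an event occurred, where feasible, remains a separate safeguard.
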